
### Intervention

A centralized randomization with stratification by age (< or ≥ 45 years) and center will be performed. It was not possible to obtain the 2 doses of aspirin (100 and 300 mg) with the same aspect; therefore, 2 different types of placebo tablets were used: one similar to the 100-mg aspirin tablet and the other similar to 300-mg tablet. Patients and investigators could identify the size of the tablet without knowing the assignment arm (aspirin or placebo). Patients are randomized to one of the four treatment conditions: aspirin 100 mg, aspirin 300 mg, placebo of aspirin 100 mg, and placebo of aspirin 300 mg, according to a ratio 1: 1: 1: 1 using a previously established randomization standardized protocol. A total blind would have required the daily intake of 2 different tablets (1 active and 1 placebo or 2 placebos). This choice was made to favor compliance by reducing the number of tablets prescribed. Patients and investigators can therefore identify the size of the tablet but without knowing the assignment arm (aspirin or placebo) (protocol version 3.0 dated 2 June 2017).

Circumstances under which unblinding is permissible are severe digestive hemorrhage, traffic accident, and another situation requiring knowing if the patient is on aspirin. The procedure for revealing a participant’s allocated intervention during the trial consists in calling the project manager or, in case of emergency, the poison control center at Fernand Widal Hospital.

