### Secondary end-points

The secondary end-points are defined as the adenomatous polyp burden (calculated as the sum of adenomatous polyps diameters as measured during planned surveillance colonoscopies); the delay between the inclusion and the first observed adenoma; the number of patients who presented with an adenoma during the follow-up according to the affected gene (MLH1, MSH2, MSH6, PMS2, other or no abnormality identified); the number of patients with sessile serrated adenoma, colon cancers diagnosed, and post-colonoscopy colon cancer (diagnosed between two planned surveillance colonoscopies); and time of apparition.

The quality of bowel cleansing, the number of chromo-colonoscopies performed in follow-up sessions, the number of remaining tablets in blisters, and side effects are reported.

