#### Visit V0

The investigator first will obtain written consent from all patients. Inclusion and exclusion criteria will be checked. The first colonoscopy will be performed no longer than 180 days before the inclusion visit to assess pre-existing lesions. Colonoscopies will be performed according to INCa (Institut National du Cancer) recommendations. Colonoscopies may be performed outside the investigator’s hospital, including any public or private institutions. All identified polyps will be removed during colonoscopies prior to the inclusion visit. During each colonoscopy, patients are scored against quality criteria as defined by the Digestive Endoscopic French Society (SFED) guidelines [19]: adequately prepared bowel (Boston ≥ 7), cecal intubation rate ≥ 90% (complete visualization of the cecum and appendicular tripod, endoscope terminal located in the proximity of the appendiceal orifice confirmed by a photo or a video), appropriate polypectomy technique (biopsy forceps removal for polyps ≤ 3 mm in size and snare polypectomy for larger polyps), and withdrawal time ≥ 6 min. Adenomatous, sessile serrated adenoma and polyp burden will also be collected.

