### Statistical methods

The initial characteristics of the population will be described globally and by group (age, sex, BMI, MSI–MLH1; MSH2; MSH6; PMS2–). The continuous variables will be described using average, standard deviation, median, minimum, and maximum. The qualitative variables will be described using frequency and percentages.

The main analysis will be done in intention of treat. A per-protocol analysis will also be performed. The statistical significance level will be 5% and all tests will be bilateral.

The main end-point analysis will be performed using logistic regression with age (< and ≥ 45 years) and using center adjustment. A specific analysis of the dose effect will be performed between the two arms of aspirin (100 mg vs 300 mg) in the case of an overall effect in the aspirin group. A subgroup analysis will be performed according to age and the *p* value was corrected according to the Bonferroni method. A center effect analysis effect will also be performed when institutes provided a small number of patients. An intermediate analysis will be carried out after 24 months of treatment on secondary judgment criteria. The Kaplan-Meier method and a log-rank test will be used to assess the effect of treatment on the delay of the appearance of the first adenoma. Patients who presented an adenoma during follow-up according to MMR status, colon cancers diagnosed, and post-colonoscopy colon cancers will be evaluated by logistic regression with age and center adjustment. Sessile serrated adenoma and adenomatous burden will be evaluated using a Poisson or a binomial regression approach.

All of the patients included in the study will be considered in the analysis. For the main analysis, lost subjects will be considered failures, regardless of the treatment group. Sensitivity analyses will also be performed, using multiple imputation methods.

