### Sample size

The main objective of this trial is to show that adenoma prevalence is less important in the aspirin group (regardless of the dose) than in the placebo group. The initial hypothesis was constructed with a 30% adenoma prevalence in the placebo group and a reduction of 28% expected in the aspirin group, based on our previous RCT on patients without Lynch syndrome but with a history of colorectal adenomas [8]. For a 5% alpha risk and 80% power, according to this hypothesis, 426 patients will be needed in the aspirin group (213 patients for aspirin 100 mg arm and 213 patients for aspirin 300 mg arm) and 426 patients in the placebo group (213 patients for placebo aspirin 100 mg arm and 213 patients for placebo aspirin arm 300 mg). A total of 852 patients will be included.

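### Adenomatous burden is a sum of diameters with no stated unit, and neither a Poisson nor a binomial regression as named suits it

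*Protocol article*

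**What the plan says.** The Secondary end-points section of the protocol article lists adenomatous polyp burden and defines it as "calculated as the sum of adenomatous polyps diameters as measured during planned surveillance colonoscopies". It gives no unit. The only polyp-size unit near the colonoscopy procedures is in the polypectomy criteria under Visit V0: "biopsy forceps removal for polyps ≤ 3 mm in size".

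The same section lists sessile serrated adenoma as a number of patients. The Statistical methods section then covers both outcomes in one sentence: "Sessile serrated adenoma and adenomatous burden will be evaluated using a Poisson or a binomial regression approach". It gives no rule for which model goes with which outcome and mentions no over-dispersion or robust variance. The general testing rule is: "The statistical significance level will be 5% and all tests will be bilateral".

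Table 3 gives a different list of key secondary outcomes. It includes a serrated polyp load at 24 and 48 months but not adenomatous burden.

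**The concern.** The named models and the defined outcome are of different types. Poisson regression is for counts and takes the variance to equal the mean. Binomial regression is for successes out of a known number of trials. A sum of diameters is neither: it is a length, zero for every patient without an adenoma and spread out among the rest.

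Two things follow if Poisson regression is run with its default variance. First, the p-value depends on whether the data file holds mm or cm, although the estimated ratio of mean burden does not. Second, in mm the variance is several times the mean, so standard errors are too small and confidence intervals too narrow. A chance difference in burden could then be reported as an effect of aspirin.

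**Working it through.** **Inputs from the article.** Two-sided 5% level (Statistical methods). Placebo prevalence 30%, relative reduction 28%, 426 patients per pooled group (Sample size). Equal allocation (Intervention). The article gives no figure for the burden analysis.

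**The article's own figure.** With p1 = 0.30 and p2 = 0.30 × 0.72 = 0.216, the usual two-proportion formula at two-sided 5% and 80% power gives 425 per group against the stated 426, and power at 426 is 80.1%. The sample size is sound, and 426 per group is used below.

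**Unit dependence (algebra, no assumptions about the data).** In a two-group log-link Poisson model with model-based variance,

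z = log(mean ratio) / √(1/S_A + 1/S_B),

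where S_A and S_B are the total burdens in the two groups. From mm to cm both totals are divided by 10. The log ratio stays the same, the standard error is multiplied by √10, and z is divided by 3.16. One dataset simulated with no true effect shows this:

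- in mm: log ratio 0.129, SE 0.052, z = 2.48, p = 0.013;
- in cm: log ratio 0.129, SE 0.164, z = 0.79, p = 0.43;
- with robust variance: p = 0.376 in both units.

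**Size of the distortion.** Let a fraction 0.30 of patients have an adenoma, and let their burden have mean m and variance s². Over all patients the mean is 0.3m and the variance is 0.3s² + 0.21m², so

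φ = variance/mean = s²/m + 0.7m.

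Poisson requires φ = 1. The true type I error is about 2[1 − Φ(1.96/√φ)]. Even if every affected patient had the same burden (s² = 0), φ would be 0.7m:

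- m = 3 mm: φ = 2.1, type I error about 18%;
- m = 5 mm: φ = 3.5, type I error about 29%.

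Real variation can only raise φ. The number of adenomas k and their diameters are not in the article, so they are assumed: k = 1 + Poisson(λ) among affected patients, and lognormal diameters rounded to whole mm. Then s² = (1 + λ)·SD² + λ·(mean diameter)². The unadjusted null simulation used 5,000 runs per scenario.

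| Mean k; diameter mean (SD), mm | m | s² | φ in mm | Type I by formula, mm | Simulated, mm | Simulated, cm | Robust, either unit |
|---|---|---|---|---|---|---|---|
| 1.0; 4 (2) | 4 | 4 | 1.0 + 2.8 = 3.8 | 32% | 32.0% | 0.2% | 5.3% |
| 1.5; 4 (2) | 6 | 14 | 2.3 + 4.2 = 6.5 | 44% | 44.5% | 1.4% | 4.8% |
| 1.5; 5 (3) | 7.5 | 26 | 3.5 + 5.25 = 8.7 | 51% | 49.5% | 3.1% | 4.5% |
| 2.0; 6 (4) | 12 | 68 | 5.7 + 8.4 = 14.1 | 60% | 59.5% | 9.4% | 4.8% |

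In cm, φ is one tenth of these values (0.38 to 1.4), which is why the same data then look mostly conservative.

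**If negative binomial was meant.** In the third scenario, 300 null datasets gave 2 rejections in mm (0.7%) and 10 in cm (3.3%), where 15 would be expected at 5%. The verdict differed between units in 8 of the 300. The test is still unit-dependent, but it errs towards missing an effect.

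**The case against.** The strongest reply is that the article names a regression approach, not a variance estimator. Robust or quasi-Poisson variance is a detail that an article may leave to an analysis plan, and it would cure both the unit dependence and the inflation. This stands as a limit: the invalid standard errors belong to Poisson regression with model-based variance, not to every Poisson fit. It does not remove the mismatch, because the article itself pairs a length with models for counts and proportions.

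Millimetres are the unit used for polyp size under Visit V0, and nothing suggests an analysis in cm. That makes a change of unit unlikely in practice. But mm is the unit in which the default test is most inflated.

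The binomial option may be a slip for negative binomial. On that reading the harm is lost power, not false positives, and the unit problem remains.

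A reader might infer that sessile serrated adenoma is mishandled too. The documents do not support this. It is listed as a number of patients, for which a binomial model is suitable.

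A reader might also infer that model and unit will be chosen after the data are seen. The article gives no selection rule, but an analysis plan that is not shown may fix both beforehand.

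**Conclusion.** The point holds for adenomatous burden, at moderate severity. As named, the binomial option cannot be fitted to a sum of diameters. The Poisson option has a valid standard error only if a robust or scaled variance is added.

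The factor of √10 in z needs no assumption beyond model-based variance. The 32% to 60% in mm and 0.2% to 9.4% in cm also rest on 30% of patients affected, on the assumed adenoma numbers and sizes, and on an unadjusted comparison. It would be tempting to say that this endpoint will be falsely significant about half the time. The documents do not support that as a general statement: it needs model-based variance, mm, and adenoma figures that the article does not give.

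The primary logistic analysis and the sample size of 852 are unaffected. Adenomatous burden is a secondary endpoint and is absent from the key secondary outcomes in Table 3, so this does not threaten the trial's main conclusion.

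**What to change.** For adenomatous burden only:

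- State the unit in the endpoint definition.
- Name one scale-invariant analysis. Suitable choices are a log-link (Poisson-type) mean model with robust sandwich variance, or a stratified rank test. The word Poisson can stay if the robust variance is stated with it.
- Adjust for age group and center, as for the other endpoints.
- If the mean model is chosen, report the ratio of mean burden with its robust confidence interval. A rank test does not give that ratio.

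Keep a binomial or logistic model for the number of patients with sessile serrated adenoma, and say which model belongs to which outcome. If the serrated polyp load in Table 3 is also a sum of diameters, analyse it in the same way as adenomatous burden.

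The cost is a few sentences and standard software, with no new data. The price is a p-value less favourable than default Poisson regression in mm would give. If an existing analysis plan already names a robust or scaled variance and the unit, saying so would be enough for the Poisson option.

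### The stated 80% power holds only if no patient is lost, because the sample size has no allowance for loss and the main analysis scores lost patients as failures

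*Protocol article*

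**What the plan says.** The Sample size section of the Protocol article sets the planning values: "The initial hypothesis was constructed with a 30% adenoma prevalence in the placebo group" and "a reduction of 28% expected in the aspirin group". It concludes: "For a 5% alpha risk and 80% power, according to this hypothesis, 426 patients will be needed in the aspirin group". The placebo group gets the same number, and the section ends: "A total of 852 patients will be included". The number needed and the number included are therefore identical, and neither an expected loss nor an inflation for it is mentioned.

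The Statistical methods section adds that "The statistical significance level will be 5% and all tests will be bilateral", that the main analysis is by intention to treat, and that every included patient is analysed. On missing outcomes it gives two rules. The main one is "For the main analysis, lost subjects will be considered failures, regardless of the treatment group". The secondary one is "Sensitivity analyses will also be performed, using multiple imputation methods".

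Under Primary end-point, the outcome is at least one adenoma at the planned colonoscopies at 24 and 48 months, so an outcome can stay incomplete over four years of follow-up.

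**The concern.** The two sections do not fit together. One sizes the trial as if every patient supplies an outcome. The other assumes that some will not, and counts each of them as having an adenoma.

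This costs more than ordinary dropout. Leaving lost patients out costs sample size but keeps the contrast between groups. Scoring them as failures keeps the sample size but dilutes the contrast, because a larger share of aspirin than of placebo patients would otherwise have been adenoma-free and can be turned into failures.

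What is at stake is the power of the primary comparison and the size of the reported effect. If loss differs between groups, the validity of that comparison is also in question.

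**Working it through.** **Inputs.** Placebo rate 0.30, relative reduction 28%, power 80% and 426 per group (Sample size); two-sided 5% (Statistical methods); allocation "according to a ratio 1: 1: 1: 1" (Intervention), which pools to 1:1 for aspirin against placebo. The loss rate L is not given, so a range of 2% to 20% is assumed.

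**Step 1: reproduce 426.** The aspirin rate is 0.30 × 0.72 = 0.216, a difference of 0.084. The mean rate is 0.258. With the pooled-variance formula:

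n = [1.960 × √(2 × 0.258 × 0.742) + 0.842 × √(0.30 × 0.70 + 0.216 × 0.784)]² / 0.084² = (1.2128 + 0.5184)² / 0.007056 ≈ 424.7, so 425 per group.

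The unpooled formula gives 422 and the arcsine formula 424. Power at 426 is 80.1%. Reading the 28% as an absolute difference, or as an odds ratio of 0.72, does not reproduce 426. The figure therefore has no slack for loss.

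**Step 2: apply the failure rule with equal loss unrelated to outcome.** Each rate becomes p′ = p + L(1 − p). The difference becomes (0.30 − 0.216)(1 − L). At L = 10%:

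- placebo: 0.30 + 0.10 × 0.70 = 0.370 (7.0 points added)
- aspirin: 0.216 + 0.10 × 0.784 = 0.2944 (7.8 points added)
- difference: 0.0756
- relative reduction: 0.0756 / 0.370 = 20%

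Power is then recomputed with 426 per group. The last column instead drops the lost patients, using n = 426(1 − L) with the planning rates.

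| Equal loss L | Placebo vs aspirin | Apparent relative reduction | Power, lost = failure | Power, completers only |
|---|---|---|---|---|
| 0% | 30.0% vs 21.6% | 28% | 80.1% | 80.1% |
| 2% | 31.4% vs 23.2% | 26% | 77.1% | 79.3% |
| 5% | 33.5% vs 25.5% | 24% | 72.4% | 78.1% |
| 10% | 37.0% vs 29.4% | 20% | 64.9% | 75.9% |
| 15% | 40.5% vs 33.4% | 18% | 57.9% | 73.4% |
| 20% | 44.0% vs 37.3% | 15% | 51.5% | 70.8% |

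At 10% loss the rule costs 75.9 − 64.9 = 11 points of power beyond the loss itself. Keeping 80% under the rule would take 512 per group at 5% loss, 609 at 10% and 838 at 20%.

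**Step 3: unequal loss with no true effect.** Both true rates are 0.30, with loss of 10% in one group and 15% in the other. The scored rates are 0.30 + 0.10 × 0.70 = 0.370 and 0.30 + 0.15 × 0.70 = 0.405, a spurious difference of 3.5 points. The test rejects in about 18% of trials in the direction of that difference, against a nominal 2.5%, and in about 0.13% in the other direction. If aspirin loses more, the error is a false harm; if placebo loses more, it is a false benefit.

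**Step 4: unequal loss with the planned effect.** With 10% loss on placebo and 15% on aspirin, the rates are 37.0% and 33.4%, a difference of 3.6 points, and power is 20%. In the reverse case the difference is 11.1 points, which overstates the true 8.4.

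**The case against.** Scoring missing outcomes as failures is a familiar and often cautious choice, and imputation is planned beside it. The trial is placebo-controlled, with allocation concealed within tablet size. Patients who stop tablets can still have the end-point colonoscopy under intention to treat, and two-yearly colonoscopy is their recommended surveillance anyway. Loss may therefore be small and balanced: at 1% power is 78.6% and at 2% about 77%. The planning rates come from an earlier trial that is not at hand, so it is unknown whether they already count lost patients as failures.

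Much of this stands as a limit on size. It does not restore the 80%. The calculation has no slack, the article does not say that its planning rates include lost patients, and imputation is only a sensitivity analysis, while the stated power belongs to the main one.

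Four stronger readings are tempting, and the documents do not support them:

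- A reader might infer that the rule adds the same block of events to both groups. It does not; equal blocks would leave the risk difference unchanged.
- A reader might infer that a patient clear at month 24 and unseen at month 48 is necessarily a failure, so that observed data are thrown away. The article does not define lost subjects, so this is one reading only.
- The 18% rejection rate might be taken as a risk of falsely claiming benefit. That is so only if placebo loses more. If aspirin loses more, it is almost entirely false harm.
- Loss might be expected to be higher on active drug. Nothing in the article shows this.

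**Conclusion.** The point holds as a mismatch between two statements that the article itself fixes, not as an omitted detail. Any non-zero equal loss takes power below the stated 80% under the plan's own main analysis. It falls to about 77% at 2% loss, 72% at 5%, 65% at 10%, 58% at 15% and 51% at 20%, and the apparent relative reduction falls with it.

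The direction needs only that some lost patients would otherwise have been counted adenoma-free in similar proportions in both groups. The size rests on the assumed loss range, on loss unrelated to outcome, on planning rates that do not already include lost patients, and on an unadjusted two-proportion test rather than the planned logistic regression. Bias from unequal loss is a supporting risk: it can go either way, and its size depends on an imbalance that the documents do not predict.

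**What to change.** In Sample size, replace the 80% with the power of 852 patients under the main-analysis rule: about 72% at 5% loss, 65% at 10% and 51% at 20%, together with the loss rate that the sponsor expects.

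Preferably also let the two planned analyses change places before unblinding. Multiple imputation, done by treatment group and using the month-24 result and baseline covariates, becomes the main analysis, and lost = failure becomes a sensitivity analysis. The completer-only powers, about 76% at 10% loss and 71% at 20%, may then be quoted as an approximate reference. They are not the power of the imputation analysis, which has not been calculated.

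Under either choice, state that an adenoma seen before loss remains an event, and state how a patient clear at month 24 but unseen at month 48 is classed.

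The cost is a change of wording and a less favourable power statement. If imputation becomes the main analysis, the primary result also rests on missing-at-random, which the failure rule as a sensitivity analysis would help to probe.

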### Sample size

The main objective of this trial is to show that adenoma prevalence is less important in the aspirin group (regardless of the dose) than in the placebo group. The initial hypothesis was constructed with a 30% adenoma prevalence in the placebo group and a reduction of 28% expected in the aspirin group, based on our previous RCT on patients without Lynch syndrome but with a history of colorectal adenomas [8]. For a 5% alpha risk and 80% power, according to this hypothesis, 426 patients will be needed in the aspirin group (213 patients for aspirin 100 mg arm and 213 patients for aspirin 300 mg arm) and 426 patients in the placebo group (213 patients for placebo aspirin 100 mg arm and 213 patients for placebo aspirin arm 300 mg). A total of 852 patients will be included.

## Discussion

Aspirin inhibits the two cyclooxygenase enzyme isoforms COX-1 and COX-2 which catalyze the rate-limiting step in the metabolic conversion of arachidonic acid to prostaglandins and related eicosanoids, leading to an inhibition of prostaglandin synthesis. COX-1 is constitutively expressed in the colon whereas COX-2 is inducible and promotes inflammation, cell proliferation, and survival. The putative anticarcinogenic effect of aspirin is therefore thought to be mainly linked to COX-2 inhibition. Aspirin irreversibly inactivates platelet cyclooxygenase in the systemic circulation, which translates into a long-lasting inhibition of platelet function. A recent study showed the role of activated platelets in colorectal tumorigenesis and dissemination through direct cell-cell interactions, lipid and protein mediators release which could be an additional target to aspirin [22]. Aspirin inhibits proliferation and induces apoptosis of cancer cells in vitro, independently of its inhibitory effect on prostanoid biosynthesis [23].

There is considerable evidence that aspirin can reduce the risk of colorectal cancer in the general population [4, 6, 8, 10–12]. However, some studies, including recently conducted randomized trials, did not characterize any protective effect of aspirin on colorectal cancer in a specific population [9, 13, 14]. Aspirin use over 4.7 years in a population of elderly, but healthy individuals, yielded an unexpected increase in the number of colorectal cancer-related deaths in contrast with previous RCT [24]. Various hypotheses have been formulated to explain these discrepancies, in particular, that biological aspirin effects may vary according to the timing of exposure, especially if undiagnosed tumors are already present which is often the case in elderly patients.

In LS patients, the randomized CAPP2 trial did not show any aspirin protective effect on colorectal adenoma or cancer incidence after a mean of 29 months, raising the suspicion that the distinct mismatched neoplastic pathway could be less susceptible to protection by aspirin [15]. However, when the follow-up reached a mean of 56 months, a significant reduction in cancer incidence was observed (1 in the aspirin group and 4 in the placebo group; IRR 0.56, 95% CI [0.32–0.99] *p* = 0.05) [16]. Confirmation of these results would strengthen aspirin’s chemopreventive potential in LS patients even if wide-spread aspirin usage is encouraged. An ongoing CAPP3 trial is exploring the optimal dose of aspirin by randomizing 3000 LS patients to 100, 300, and 600 mg/day but without considering a placebo group. The AAS-Lynch trial could contribute to these evaluations and also determine the most effective dose between 100 and 300 mg conditions. Aspirin’s chemopreventive effect could contribute to the reduction in the burden of endoscopic surveillance in Lynch patients according to different germline alterations in mismatch repair genes. The AAS-Lynch trial will report high-quality colonoscopy details and will allow delineating such a benefit. Long-term aspirin safety is already known [25] but has been reevaluated in this specific population [25]. Furthermore, this study will also allow describing compliance with respect to chemoprevention by daily aspirin therapy in Lynch syndrome patients.

The gut microbiota is a complex community consisting of bacteria, fungi, protozoa, viruses, and bacteriophages which live in a symbiotic and epigenetic relationship with the host. Gut microbiota can promote either health or tumor progression through its inflammatory and proliferative effects, depending on the context and genetic factors of the host. Specific microorganisms or variability of the microbiota have been recently associated with CRC but how gut microbiota contributes to CRC pathogenesis in the host is not fully understood. This prospective study design would account for the nutritional habits of the population, include validated questionnaires, and collect stool samples in order to investigate to the role of microbiota in colorectal carcinogenesis.

